### Participants and Recruitment

#### Eligibility Criteria for Participants

Eligibility criteria were as follow: (1) male or female and aged 40-74 years, inclusive, (2) prescribed a statin medication for primary prevention of CVD that was still active, at least 12 months prior to enrollment, (3) total cholesterol level ≥5.0 mmol/L at enrollment, (4) able to speak and read English to participate effectively in the group education program, (5) willing and able to attend education sessions and clinic visits, (6) access to a mobile phone, (7) willing and able to give informed consent, (8) willing to allow their GP to be notified of participation in the study, (9) no preexisting CVD, (10) no inherited lipid disorder, (11) no established type 1 or type 2 diabetes, (12) no women who were pregnant (self-reported), and (13) no participation in another clinical intervention study in the 12 weeks prior to enrollment.

As we expected there to be participants who had repeat prescriptions for statins but were not taking them as directed, we considered a prescription to be active, for the purpose of the study, if the prescription had been issued at least twice within the previous 2 years. We recruited participants with a total cholesterol level of 5 mmol/L or greater at baseline, based on the assumption that these participants were more likely to be nonadherent to statin medication if their cholesterol levels were higher.

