### Control Group

The control group continued with their usual GP care with regard to lifestyle and medication advice for the primary prevention of CVD. To ensure that all participants had access to at least some basic knowledge about managing CVD risks, we sent both groups a British Heart Foundation booklet (*Keep Your Heart Healthy*), which contained general information about CVD risk prevention.

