#### Delivery of the 3R Education Program and Follow-Up Support

We invited the intervention group to attend the 3R Education Program and receive the follow-up support (text messages and phone calls). They continued with their usual GP care and were sent a copy of the British Heart Foundation booklet. Textbox 1, Textbox 2, and Textbox 3 detail the different components involved in the delivery of each of the 3 major elements of the intervention and identify the behavioral control techniques [29] or active components involved in each.

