### Statistical Methods

For evaluation, we will summarize baseline characteristics of the 2 groups with means, standard deviations, and medians and ranges for continuous variables; and counts and percentages for categorical variables. Logistic regression will assess the difference in medication adherence by group, adjusted for the stratification factors (sex and age) at 12 months. We will assess the primary outcome at the 5% level with 95% confidence intervals. The primary analysis at 12 months will be based on complete data. The analysis of the secondary outcomes will be conducted in a similar manner using the appropriate model type: logistic regression for binary outcomes, linear for continuous outcomes, and ordinal for ordinal outcomes.

We will carry out sensitivity analyses on an intention-to-treat basis and a per-protocol basis to examine robustness of conclusions for missing data and attendance of the program. To adhere to the intention-to-treat principle, we will impute missing outcome data by multiple imputation using the command MI in Stata (StataCorp LLC). We will also conduct analysis by adding the MMAS adherence data where urine adherence data are missing.

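### The per-protocol check on programme attendance can exclude people from one arm only, so its agreement with the primary result would be weak evidence of robustness

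*Protocol article*

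**What the plan says.** Under Statistical Methods, the article sets the main model: "Logistic regression will assess the difference in medication adherence by group, adjusted for the stratification factors (sex and age) at 12 months". On the analysis set it says: "The primary analysis at 12 months will be based on complete data". Neither statement removes anyone for not attending.

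Sensitivity analyses follow, on an intention-to-treat basis with multiple imputation and on "a per-protocol basis to examine robustness of conclusions for missing data and attendance of the program". Read in order, imputation addresses missing data and the per-protocol analysis addresses attendance. The article does not say how many sessions count as attendance, how controls are treated, or whether this analysis has covariates beyond sex and age.

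The two arms differ in what they could attend. Under Delivery of the 3R Education Program and Follow-Up Support: "We invited the intervention group to attend the 3R Education Program and receive the follow-up support". Under Control Group: "The control group continued with their usual GP care with regard to lifestyle and medication advice". Both arms were sent the same booklet.

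**The concern.** Controls had no sessions, so no attendance rule can exclude a control. The intervention arm would be cut down to those who chose to come, while the control arm would still contain people who would not have come if invited. Randomisation no longer balances the two sets.

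This matters more here than in many trials because the outcome, statin detected in urine, is a health behaviour. Attending two sessions of about two hours each plausibly goes with taking tablets. Sex and age are unlikely to account for that. Baseline urine adherence, a far more relevant covariate, is collected (Table 1) but not named in the model.

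A sensitivity analysis is useful only if agreement with the primary result carries information. If the likely bias favours the intervention, agreement with a positive primary result says little, and a better-looking result beside a null primary one could mislead.

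**Working it through.** **Inputs from the article.** The Sample Size section gives 84 analysed per group, 80% power, 5% significance, rates of 91% and 74%, and a stated 16-point difference.

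**The plan's own figure.** 84/(1 − 0.20) = 105 per group, and 2 × 105 = 210; both match. The 84 is reproduced by the usual two-proportion formula (pooled, two-sided) once rounding of the rates is allowed for. Rates such as 90.6% and 74.2% give exactly 84; the printed pair 91% and 74% gives 78. Nothing below depends on this beyond using 84 per arm and 74% adherence as a realistic setting.

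**Assumptions.** The article gives neither of these, so a range is shown:
- a = share of the intervention arm that attends: 60% to 90%
- g = adherence gap, attenders minus non-attenders: 0 to 30 points

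**Spurious difference with no true effect.** Let p be adherence in both arms, and p_A and p_N adherence in attenders and non-attenders.

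p = a·p_A + (1 − a)·p_N and p_N = p_A − g, so p_A − p = (1 − a)·g.

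Example: a = 0.80, g = 0.20, p = 0.74. Then p_A = 0.74 + 0.20 × 0.20 = 0.78 and p_N = 0.58. Check: 0.8 × 0.78 + 0.2 × 0.58 = 0.74. Attenders against all controls shows 78% v 74%, a 4-point benefit from nothing.

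**Chance of a significant result favouring the intervention when there is no effect.** Nominal 2.5%; two-proportion z test, 84 controls, intervention arm restricted to attenders, 200,000 simulated trials per cell. Each cell gives the spurious difference, then the chance.

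| Attendance | g = 10 | g = 20 | g = 30 |
|---|---|---|---|
| 90% | 1 pt, 3.5% | 2 pt, 4.8% | 3 pt, 6.4% |
| 80% | 2 pt, 4.6% | 4 pt, 8.1% | 6 pt, 13.4% |
| 70% | 3 pt, 5.8% | 6 pt, 12.5% | 9 pt, 24.0% |
| 60% | 4 pt, 7.1% | 8 pt, 17.6% | 12 pt, 37.1% |

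With g = 0 the chance stays at about 2.5%. The as-randomised comparison stays at 2.5% to 2.6% in every cell.

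**The alternative.** Controls have no access to the programme, so non-compliance is one-sided and, without covariates, the complier-average effect is (difference between arms as randomised)/a. With no true effect the numerator is centred on zero, so the estimate is too, whatever g is.

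Its price is precision. At p = 0.74 with 84 per arm, the as-randomised standard error is √(2 × 0.74 × 0.26/84) = 6.8 points. At a = 0.80 the complier-average standard error is about 6.8/0.80 = 8.5 points. The attenders-only standard error is √(0.78 × 0.22/67.2 + 0.74 × 0.26/84) = 7.0 points, where 67.2 = 0.80 × 84.

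**Where the exclusion restriction bites.** The method assumes that people classed as unexposed gain nothing from allocation. Suppose, for illustration, that 70% attend both sessions, a further 20% receive one session, texts or calls, and all 90% gain the same effect e. The as-randomised difference is 0.9e. Dividing by 0.7 gives 1.29e, an overstatement; dividing by 0.9 gives e. The threat comes from unexposed people who did receive something. If non-attenders receive nothing at all, the restriction is easier to defend.

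**The case against.** Four points can be made for the plan.

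- **The comparison is not spelled out.** A reader might take it as stated that attenders are compared with every control. The article says only that the analysis is per protocol. The detailed definition is commonly left to a full protocol or analysis plan, and its absence here is no fault. This stands, and the comparison is therefore described as the natural reading. One part needs no inference: controls cannot fail an attendance rule for a programme they were not offered.
- **It is only a sensitivity analysis.** A reader might infer that it could rescue a null trial. The plan gives it no such role. The primary analysis does not exclude anyone for non-attendance, and neither does the imputed intention-to-treat analysis. This stands in full; over-reading the per-protocol result would be a reporting failure that the plan does not provide for.
- **The bias may be small.** Participants had to be "willing and able to attend education sessions and clinic visits", which may keep attendance high; at 90% attendance and a 20-point gap the bias is 2 points. This stands as a limit on size. It does not remove non-attendance, since the plan itself provides for an attendance analysis and tracks retention over the two sessions.
- **A complier-average effect answers a different question and has its own assumption.** True. That is a reason to state the assumption and to allow the conventional analysis to stay beside it. Deleting the per-protocol analysis is not required.

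**Conclusion.** The concern holds in a limited form. The per-protocol analysis is the plan's tool for judging robustness to attendance, and it is open to selection bias, probably in favour of the intervention. With a 20-point gap, the spurious benefit runs from 2 points at 90% attendance to 8 points at 60%, against a 16-point planning difference. The chance of a falsely significant benefit runs from 4.8% to 17.6%, against a nominal 2.5%. These sizes rest on assumed attendance and an assumed gap. The bias is zero if all attend or if attending is unrelated to adherence, and it would reverse if non-attenders were the better tablet takers.

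It would go too far to say that the analysis cannot inform on attendance at all, or that it is certain to favour the intervention: the article supplies neither of the two quantities that decide this. The primary conclusion is untouched.

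**What to change.** Make the attendance analysis a complier-average causal effect with randomised allocation as the instrument, for example by two-stage least squares on the risk-difference scale, adjusted for sex, age and baseline urine adherence.

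Define exposure in two steps:
1. Receipt of any intervention component (a session, texts or calls; the booklet does not count because both arms were sent it). The exclusion restriction is most defensible here.
2. Attendance at both sessions, with a note that one-session attenders, or non-attenders who received texts or calls, would breach the restriction.

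If the per-protocol comparison is kept, label it supportive and open to selection bias, and add baseline urine adherence to its covariates.

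The cost is small. Under Process Outcomes the article records session retention, text-message logs and all attempted calls, and under Results it says that analysis had not yet started. The change is wording plus one standard analysis. The downsides are a wider confidence interval, by a factor of roughly 1/attendance relative to the as-randomised comparison, and reliance on the exclusion restriction.

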**Figure 1 figure1:**
[figure not shown]
Study design. CVD: cardiovascular disease; GP: general practitioner.

Reply slips (from both positive and negative responders) were returned directly to the research team. We contacted all positive responders to verbally screen and confirm their eligibility for the study. Following this, eligible patients who were interested in taking part were booked to attend an initial data collection clinic. All participants were required to attend 2 data collection clinics: at baseline and at 12 months. The clinics were held in a suitable local venue, usually a community venue. Group clinics (of up to 8 participants at a time) were run by 3 trained study staff, including a qualified nurse. A full patient information sheet was sent with the clinic appointment letter. At the baseline clinic, written informed consent for all participants was taken by a trained research nurse before the collection of any data. All participants were made aware that they could withdraw from the study at any time. For each participant, a blood sample and clinical measurements were taken in accordance with local standard operating procedures, and a urine sample was collected. A hardcopy questionnaire booklet was completed at clinic by each participant. In addition, a hardcopy clinical research form was used to enter all other data collected at the baseline and 12-month time points, including demographic data, medical and medication histories, clinical measurements, blood results, and adverse events. Following clinics, all hardcopy study data collected were treated as confidential and kept securely in locked cabinets. Study data were anonymized and participants were identified by an allocated study number. These hardcopy data were then manually entered onto a validated, secure, and password-protected electronic database to be checked and verified prior to analysis.

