**Other supporting outcomes^e^**				
	Prescription history	Record of repeat prescription issues for statins and antihypertensives (if applicable) from the GP database	✓	✓
	Adverse events	Self-report and observed from GP database	✓	✓

^a^N/A: not applicable.

^b^GP: general practitioner.

^c^TC: total cholesterol.

^d^HDL: high-density lipoprotein.

^e^For the duration of the study.

^f^Use of the MMAS is protected by US and International copyright laws. Permission for use is required. A license agreement is available from: [name], MMAS Research (MORISKY), [name]; [contact].

In addition, the self-reported 8-item Morisky Medication Adherence Scale (MMAS) was completed at baseline and 12 months. This is an established and validated scale that is commonly used to measure adherence [37,50,51]. At the end of the study, we asked GP practices to provide details for individual participants regarding both statin and antihypertensive (if applicable) prescription issued during the 12 months of the study (Table 1). These data will provide useful supporting information about the pattern of patient medication adherence behavior over the 12-month study period.

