### Sample Size

The primary outcome measure was medication adherence to statins at 12 months. We based the sample size calculation on the percentage of nonadherers by using data from the Investigation of Text Message Reminders on Adherence to Cardiac Treatment (INTERACT) trial [32]. To detect a difference in the proportion of medication adherers (of 16 percentage points in the intervention group at 12 months compared with the usual-care control group—ie, 91% compared with 74%), we required 84 participants per group with 80% power and 5% significance. After allowing for a 20% dropout, we required 105 participants per group, making 210 participants in total. This minimum difference was based on a similar 16 percentage–point increase in adherence to cardiovascular preventive treatment observed in the INTERACT trial [32], which used text messaging as the sole intervention. This was a 6-month follow-up study with a final control group adherence of 75%. We envisaged similar adherence to medication at 12 months’ follow-up, following our complex intervention with continued follow-up support via SMS text messaging and phone calls to sustain any initial intervention effect.

The study design was pragmatic and reflected how it would be delivered if it were implemented in practice. The study was designed to mitigate the effects of unbalanced clustering in the intervention group by using a standardized curriculum, a small group of trained facilitators to deliver education and phone calls, a small number of venues, standardized text messages, and standardized phone calls. Moreover, we assessed process outcomes relating to fidelity to allow for clear reporting of any variation that occurred. This was in line with the Medical Research Council guidance for complex interventions [26].

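### As described, the missing-data checks do not explore informative dropout: the MMAS fill cannot reach people who miss the 12-month clinic, and the imputation rests on missing at random

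*Protocol article*

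**What the plan says.** All references are to the protocol article.

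- **Statistical Methods.** The primary analysis is logistic regression of 12-month adherence on group, adjusted for sex and age, in participants with complete data. Sensitivity analyses on an intention-to-treat and a per-protocol basis are planned "to examine robustness of conclusions for missing data and attendance of the program". Missing outcomes are to be imputed with Stata's MI command; the imputation model is not given. The paragraph ends: "We will also conduct analysis by adding the MMAS adherence data where urine adherence data are missing".
- **Method of Recruitment** (text after Figure 1). "A hardcopy questionnaire booklet was completed at clinic by each participant".
- **Primary Outcome.** The urine sample is a first-morning sample that the participant provides ahead of the clinic. After Table 1 the MMAS is described as completed at baseline and 12 months. The same text says "we asked GP practices to provide details for individual participants regarding both statin and antihypertensive (if applicable) prescription issued during the 12 months", and treats these records as supporting information on adherence.
- **Secondary Outcomes.** All outcome measures are collected at the baseline and 12-month clinics.
- **Sample Size.** "After allowing for a 20% dropout, we required 105 participants per group". This is the only figure the article gives for missing data.

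**The concern.** Urine and MMAS come from the same visit. Someone who does not attend at 12 months lacks both, together with the blood results, blood pressure and other questionnaires from that day. The MMAS fill therefore works only for attenders with no usable urine result. If the 20% allowance is mainly people lost before the 12-month clinic, it is mainly a group that the fill cannot touch.

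The other check is multiple imputation. In its ordinary form it assumes that, given the variables in the model, those with missing outcomes adhere like those observed. No stated analysis departs from that assumption. The one requested adherence record that covers both arms after randomisation without needing the 12-month clinic is the GP record of statin issues, and Statistical Methods gives it no role in handling missing urine results.

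This matters because the trial is open, participants know that the urine is tested for statins, and only one arm receives sessions, calls and texts. Reasons for dropping out may well relate to adherence and differ by arm. The complete-case, imputed and MMAS-filled results could then agree closely and be reported as robust, although the assumption they share was never varied.

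**Working it through.** **1. The plan's own figure.** 84 / (1 − 0.20) = 105 per group, 210 in total. This reproduces the article. It allows for 105 − 84 = 21 missing per group.

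**2. Size of the possible bias.** Let *m* be the dropout fraction, equal in both arms, and let Δ be adherence in completers minus adherence in dropouts. Then:

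complete-case difference − true difference = *m* × (Δ_intervention − Δ_control)

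Inputs: *m* = 0.20 and 91% from Sample Size, and a 75% control rate. The section prints 91% v 74% but calls the gap 16 points; 75% is its quoted control rate from the source trial and gives exactly 16. Dropout adherence is assumed.

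| Dropouts: intervention / control | True difference | Complete-case | Error |
|---|---|---|---|
| 75% / 75% | 0.8×0.91 + 0.2×0.75 − 0.75 = 12.8 | 16 | +3.2 |
| 83% / 75% | 0.894 − 0.75 = 14.4 | 16 | +1.6 |
| 91% / 59% | 0.91 − (0.8×0.75 + 0.2×0.59) = 19.2 | 16 | −3.2 |

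So the error can have either sign. With 74% in place of 75% throughout, the first row becomes 0.876 − 0.74 = 13.6 against 17, an error of +3.4. On the odds-ratio scale of the planned model, ignoring sex and age, the first row is (0.91/0.09)/(0.75/0.25) = 3.37 among completers against (0.878/0.122)/(0.75/0.25) = 2.40 in truth.

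**3. Does imputation correct it?** In a simulation of the first row (4000 per arm, 60 replicates, 10 imputations), one run gave 16.0 points for complete-case, 16.0 for imputation on arm, sex and age, and 12.9 for the full data.

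A second large-sample comparison used other assumed rates, with about 20% missing and a true difference of 17.0 points:

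| Missingness depends on | Complete-case | MI: arm | MI: + baseline urine | MI: + baseline urine + GP issues |
|---|---|---|---|---|
| nothing | 17.0 | 17.0 | 17.0 | 17.0 |
| baseline adherence (truth 17.1 in this run) | 15.9 | 15.9 | 17.1 | 17.1 |
| 12-month adherence, intervention arm only | 21.6 | 21.6 | 21.4 | 20.6 |
| 12-month adherence, both arms | 11.9 | 11.9 | 12.7 | 14.1 |

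Baseline urine repairs the estimate where missingness depends on baseline adherence, and does little otherwise. The last row concerns the risk difference. When dropout depends on adherence identically in both arms, the odds ratio is preserved (about 3.5 with and without dropout at these rates), so differential dropout is the main threat to the logistic model.

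**4. Does the MMAS fill correct it?** In the intervention-arm case the filled estimate is 21.6 if none of those with missing urine attended, 21.0 if 10% did and 19.1 if 50% did (assumed MMAS sensitivity 0.9, specificity 0.6). With 50% attending it also moves 17.0 to 16.1 when missingness is random. A shift therefore partly reflects MMAS misclassification and is not evidence about dropouts.

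**5. How much does the GP record add?** Take the first row of step 2, with 95% of adherers and a fraction *q* of non-adherers having a current issue. For *q* = 0.6:

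- Completers: P(adherent | issue) = 0.91×0.95 / (0.91×0.95 + 0.09×0.6) = 0.941; P(adherent | no issue) = 0.0455 / (0.0455 + 0.036) = 0.558.
- Dropouts: P(issue) = 0.75×0.95 + 0.25×0.6 = 0.8625.
- Imputed adherence in dropouts: 0.8625×0.941 + 0.1375×0.558 = 0.889, against 0.91 without the record and 0.75 in truth.
- Bias removed: (0.91 − 0.8886) / (0.91 − 0.75) = 13%.

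The same steps give 44% for *q* = 0.2, 8% for 0.7, 3% for 0.8 and 0.4% for 0.9.

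**6. What it could do to the conclusion.** Assume 106 per arm (212 randomised 1:1), 85 observed in each, 77 v 63 adherent: 16.5 points, p = 0.005. With dropouts 50% adherent in the intervention arm and 74% in control, the difference is 8.5 points, p = 0.14. With all dropouts counted non-adherent it is 13.2 points, p = 0.042. These p-values treat filled-in values as observed.

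**The case against.** The strongest reply is that the article does not give the imputation model. Auxiliary variables and any not-at-random runs commonly sit in the full protocol or SAP, which are not shown. Baseline urine is collected, and nothing bars it or the GP record from the model. This stands. A reader might infer that imputation must reproduce the complete-case result; the documents do not support that, since it follows only if the model is limited to arm, sex and age.

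A reader might also infer that neither check brings any information from after randomisation. That goes too far. The sample is brought from home, so an attender can lack one, and for that person the 12-month MMAS is new information. The article neither calls the MMAS fill a dropout check nor defines dropout as clinic non-attendance.

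Nor do the documents show that the effect would be inflated: step 2 gives either sign. And no analysis of the observed data can detect or exclude informative dropout. A shift analysis explores it without detecting it.

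Finally, the GP record may discriminate poorly. The Eligibility Criteria section itself expects some participants to hold repeat prescriptions without taking the drug as directed, and entry required recent issues. That also stands, and it is why the record cannot be the main remedy.

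None of this alters where the MMAS is collected, or that the stated checks, as described, leave informative dropout unexamined.

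**Conclusion.** The concern holds in a limited form. From the article alone, the MMAS fill cannot inform on people who miss the 12-month clinic, the other stated check is ordinary missing-at-random imputation, and the GP issue record has no stated part in either. The robustness the article sets out to examine is therefore not examined for informative dropout, as far as it describes.

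The illustrative size is 3.2 points of a 16-point difference (20% of it) if intervention dropouts adhere at the control rate, and 1.6 points (10%) if they adhere at 83%. The sign reverses if control dropouts are the worse group. These figures rest on 20% dropout in each arm and on assumed dropout adherence; the article gives no data on the latter. This is a worthwhile improvement to the sensitivity analyses, not a demonstration that the primary result is biased.

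**What to change.** In Statistical Methods, or in the SAP if it is still open (the Results section says analysis had not begun):

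1. Add an arm-specific shift (tipping-point) analysis to the planned imputation. Vary the log-odds of adherence among those with missing outcomes, separately in each arm, until the conclusion changes. Include the case of intervention dropouts adhering at the control rate.
2. Name the auxiliaries in the imputation model: the baseline urine result, and the GP statin-issue record over the 12 months with its interaction with arm (for example, whether an issue covered the date the final visit was due). State that the record is expected to remove only part of any bias.
3. Describe the MMAS fill as covering attenders without a usable urine result, and not as a check on dropout. Report how many participants it reaches in each arm.

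The cost is wording and a few more runs of an imputation already planned. The GP data are already requested. Intervals may widen slightly, and GP records may be missing for anyone who withdrew permission to use them.
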